## Methods

### Overview

Our team will conduct a naturalistic study of the IACP for youth with EDs that will gather 3 types of data. First, the feasibility of the IACP will be evaluated using recruitment, retention, and adhesion-to-protocol rates. Second, the acceptability of the IACP program and web-based delivery method among youth participants will be measured using youth and parent satisfaction questionnaires. Finally, the preliminary effectiveness of the IACP will be described using quantitative self-report questionnaires pertaining to ED symptomatology, and several moderators of this effect will be investigated. Body mass index (BMI) and quantitative self-report measures of comorbid psychopathology will be used as secondary outcome measures to describe the preliminary effectiveness of the intervention in an uncontrolled naturalistic setting.

### Population

Individuals eligible for the study will be between 12 and 18 years of age, have a diagnosed ED according to the DSM-5 (Diagnostic and Statistical Manual of Mental Disorders, Fifth Edition) criteria [40], and will already have received medical treatment in the hospital or ambulatory setting at our specialized ED clinic. This clinic is located in a tertiary pediatric hospital in a large city in the province of Quebec, which serves both a multicultural urban population representative of other large cities in North America in addition to the surrounding suburban and rural populations. Individuals who meet these criteria will be invited to participate in the IACP and the current research. To be eligible for the IACP, individuals must be available to participate in all aspects of the proposed intervention (including pre- and postintervention measures, individual, family, and group sessions, and an intake and feedback meeting with the IACP clinical team).

Individuals will be excluded from the IACP (and the current research study) if they require hospitalization for medical stabilization when evaluated for recruitment. In addition, the intervention will be discontinued and the individual referred to the appropriate service if they become medically unstable during the program (eg, heart rate <45 bpm, body temperature <35.5 °C) or express acute psychiatric distress (eg, active suicidal ideation requiring hospitalization).

### Recruitment, Enrollment, and Consent

Clinicians working in ambulatory and hospital settings at our specialized ED clinic will refer patients who are suitable for the IACP. These patients will be screened for eligibility by an IACP clinical coordinator. All patients who meet the criteria for participation in the IACP will receive a brief explanation of the study during the initial screening meeting with the clinical coordinator and will be presented with the opportunity to meet a research assistant to discuss consent if they are interested in participating in the research study. It will be made clear that participation in the research study is optional and that it will not affect any care or services received in the IACP.

The meeting with the research assistant will take place with the eligible participant and at least one parent, either in-person or via the secure Teams videoconferencing platform. The research assistant will verbally explain the objectives of the study, the main procedures involved, and the potential benefits and risks of participation. The participant and their parents will be given time to ask questions and consider participating. If they agree, a consent form (summarizing the verbal explanation of the study) will be presented to them for both parents and participants to sign.

Recruitment will occur on an ongoing basis over the 2-year study period. We expect that approximately 100 patients will be recruited (see the section on power calculation below for more details).

### Attrition and Compliance

We expect to recruit approximately 80% (100/120) of eligible participants—that is, 80% of all youth enrolled in the IACP—to our study, which is a conservative estimate based on previous literature [41]. Participation in the research study entails no additional commitment from eligible participants, given that all study materials are also an integral part of the IACP. Further, we expect attrition to be less than or equal to 25% (25/100), based on the current literature, which suggests a 7% to 42% dropout rate for adolescents enrolled in day treatment programs for the treatment of EDs [17,42-45], and also considering the flexible, modular, and hybrid nature of our program, which may allow us to improve retention rates.

Participants who attend at least one session per week of treatment in the IACP (and complete both pre- and postintervention materials) will be considered sufficiently exposed to the intervention and, thus, will be included in the data analysis on the preliminary effectiveness of the program.

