Adherence to protocol	At least 70% (70/100) of participants complete at least one therapeutic session per week of treatment in the IACP. At least 70% (70/100) of participants complete all pre- and postintervention questionnaires. At least 70% (70/100) of participants complete at least one therapeutic session per week and all pre- and postintervention questionnaires.

^a^IACP: Intensive Ambulatory Care Program.

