### Statistical Analysis

Statistical analyses will be performed using SPSS version 27.0. Feasibility and acceptability will be analyzed by summarizing quantitative data from (1) clinician-reported recruitment rate, retention rate, and adherence to protocol using descriptive statistics; (2) weekly satisfaction surveys of individual and group activities; and (3) postintervention surveys of overall satisfaction and satisfaction with the web-based mode of intervention. Qualitative data from both the weekly and overall satisfaction surveys will be analyzed using conventional content analysis. Patient characteristics at baseline will be summarized using descriptive statistics.

The preliminary effectiveness of the IACP intervention will be examined using general linear mixed models, with changes in global EDE-A scores from baseline to the end of treatment as the primary outcome. Appropriate covariates (eg, number of attended sessions) and random factors (eg, therapist) may be added to the statistical model for exploratory analysis. Similar general linear mixed model analyses will be run for the secondary outcome measures (Table 3), comparing scores from the baseline to the end of treatment. Finally, general linear mixed models will also be used to study the moderating role of the level of attendance and other clinical and psychosocial factors such as age, length of illness, ED diagnosis (anorexia nervosa vs other types of ED), and family connectedness on the primary outcome (change in EDE-A scores from baseline to end of treatment).

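### The only effectiveness analysis set described is defined by attendance and questionnaire completion after baseline, so the pre-post EDE-A improvement may be overstated for adolescents who enter the IACP

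*Protocol article*

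**What the plan says.** Attrition and Compliance sets the rule. "Participants who attend at least one session per week of treatment in the IACP (and complete both pre- and postintervention materials") count as adequately exposed and on that ground enter the effectiveness analysis: they "will be considered sufficiently exposed to the intervention and, thus, will be included in the data analysis on the preliminary effectiveness of the program".

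Statistical Analysis names the model as "general linear mixed models, with changes in global EDE-A scores from baseline to the end of treatment as the primary outcome". It gives no wider analysis set.

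Three other parts of the article bear on who fails the rule:

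- **Population:** "the intervention will be discontinued and the individual referred to the appropriate service if they become medically unstable during the program". The same applies to acute psychiatric distress.
- **Table 1 (Data Collection):** the joint adherence target is "At least 70% (70/100) of participants complete at least one therapeutic session per week and all pre- and postintervention questionnaires". This is in substance the inclusion rule. Separately, "we expect attrition to be less than or equal to 25% (25/100"), set against literature "which suggests a 7% to 42% dropout rate for adolescents enrolled in day treatment programs".
- **Anticipated Outcomes:** the authors expect that more participation will go with a larger fall in symptoms.

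Objectives and Hypotheses and Statistical Analysis also plan level of attendance as a moderator of response.

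**The concern.** Both conditions for inclusion are met or failed after baseline, and the article itself gives reasons to link them to outcome. A participant stopped for instability or acute distress is deteriorating and is unlikely to satisfy both conditions. A low attender is, on the authors' own expectation, someone who improves less. Leaving both groups out would move the mean change in the programme's favour. Because the trial is an uncontrolled pre-post comparison, no second arm carries a similar selection that might cancel it.

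At stake is what the effectiveness result describes. The anticipated medium-sized reduction would be a figure for adherent completers, yet the Abstract and Future Implications would use it to judge the programme as a whole and its spread to other sites. The limitations section does not mention this selection.

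The rule has two further costs. It discards end-of-treatment EDE-A scores that low attenders did supply. It also removes part of the low end of the attendance range, which the plan then wants to study as a moderator.

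**Working it through.** **Inputs from the article.** Joint adherence target 70/100; accepted loss 25/100; literature dropout 7% to 42%. The power section expresses a medium effect only as f² = 0.15.

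**Assumption.** A mean change of -0.50 SD in those analysed. The article gives no such figure, so only the relation between the numbers below matters.

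**Step 1: how many can be left out.** The inclusion rule and the joint target coincide, so with the target just met, 100 - 70 = 30 participants are outside the effectiveness analysis. If 25 are also lost to follow-up and all of them fail the rule, then 30 - 25 = 5 of those left out were retained and may have end-of-treatment data that go unused.

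**Step 2: mean for all enrolled.** With p the share analysed,

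all-enrolled mean = p × (mean in those analysed) + (1 - p) × (mean in those left out).

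| Left out of 100 | Change equally (-0.50) | Half the change (-0.25) | No change | Worsen by 0.25 |
|---|---|---|---|---|
| 7 | -0.50 | -0.48 | -0.465 | -0.45 |
| 25 | -0.50 | -0.44 | -0.375 | -0.31 |
| 30 | -0.50 | -0.425 | -0.35 | -0.275 |
| 42 | -0.50 | -0.395 | -0.29 | -0.185 |

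For the 30 row: 0.70 × 0.50 = 0.35, and 0.70 × 0.50 - 0.30 × 0.25 = 0.275. The completer figure would then be 0.50/0.35 = 1.43 or 0.50/0.275 = 1.82 times the all-enrolled figure. In the first column the ratio is 1.

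**Step 3: the same question with a selection model.** Suppose the true improvement is 0.50 SD (of the change) and completion correlates ρ with improvement. The completer mean is 0.50 + ρ × φ(z)/p, with z = Φ⁻¹(1 - p). At p = 0.70 the multiplier φ(z)/p is 0.497. This gives 0.50, 0.60, 0.65 and 0.75 for ρ = 0, 0.2, 0.3 and 0.5. At p = 0.75 the figures are 0.50, 0.59, 0.63 and 0.71.

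**Step 4: does a mixed model on all baselines repair it?** The simulation assumed a true change of -0.50 SD of the score, T0-T1 correlation 0.6, about 28-31% left out and contributing a baseline only, and log-odds of exclusion from 0.5 to 1.5 per SD of worsening.

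| Selection | Completer mean | Likelihood model, all baselines | Share of bias removed |
|---|---|---|---|
| weakest | -0.605 | -0.584 | 0.021/0.105 = 20% |
| middle | -0.700 | -0.664 | 0.036/0.200 = 18% |
| strongest | -0.775 | -0.728 | 0.047/0.275 = 17% |

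With two time points, a baseline alone says little about change. Most of the gain must come from observed end-of-treatment scores.

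The sample-size figures (68 and 98) do not enter this point.

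**The case against.** The strongest reply is that the primary objective is feasibility and acceptability. Effectiveness is a secondary, descriptive aim of a pilot, the set is openly labelled as sufficiently exposed, and retention and adherence are reported on all enrolled, so the fraction left out will be visible. This stands, and it lowers the severity. It does not make the completer mean a programme-level estimate.

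Several stronger readings are tempting, but the article does not support them:

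- **That the improvement is overstated, by 43% or 82%.** Those figures come from assumed outcomes in people not observed. Usual outpatient care continues outside the IACP (Intervention), so no change is not the natural default. If those left out improve as much as those kept, there is no bias.
- **That unstable participants are always dropped.** The intervention is stopped, but nothing says the person leaves the study or may not complete the post measures. The rule does not say that only qualifying participants are analysed, and it is unclear whether a session is needed in every single week. Exclusion is the natural reading of the stated ground for inclusion, but it is a reading.
- **That the model is a change-score model that wastes baselines.** The wording "with changes in global EDE-A scores from baseline to the end of treatment as the primary outcome" can simply name the contrast. Study Design speaks of within-participant comparison, and the secondary outcomes compare scores from baseline to end of treatment; both fit repeated T0 and T1 responses. Step 4 also shows that this choice alone matters little.
- **That the attendance moderator cannot be studied.** The cut of one session is below the planned minimum of two to three a week, and the hypothesis is framed in hours attended, which still vary above it. The truncation is partial.

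**Conclusion.** The point holds as a stated rule that gives a worse answer than an available alternative. The article fixes a completer set as its only described effectiveness set. Its own discontinuation criteria and its own expectation about participation make bias in the programme's favour the likely direction. Up to 30 of 100 participants can be left out with the adherence target met.

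The size is unknown. On the assumption of -0.50 SD in those analysed, the all-enrolled mean runs from -0.50 SD (equal change) through -0.35 SD (no change) to -0.275 SD (worsening by 0.25 SD) at 30 left out. These are illustrations and not estimates. Unused end-of-treatment data and the partly truncated attendance range are lesser, additional costs.

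Severity: should be fixed. Feasibility and acceptability, the primary objective, are not affected.

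**What to change.** 1. Make the main effectiveness set all enrolled participants with a baseline EDE-A, regardless of attendance. Fit the mixed model already planned with the T0 and T1 scores as repeated responses.
2. Still request the existing end-of-treatment EDE-A from participants who stop early, where feasible. This matters most, because scores not collected at the time cannot be recovered later.
3. State that with two time points the likelihood model alone recovers little, and add one simple sensitivity analysis for those without T1, for example zero change.
4. Keep the present set (weekly attendance plus both sets of materials) as a labelled per-protocol sensitivity analysis.
5. Examine attendance as a moderator in the full set, so that low attenders with T1 data contribute.

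**Cost.** The change needs new analysis wording and one extra analysis. The EDE-A takes 7-8 minutes by Table 3, so the follow-up effort is small, but it is real. The article says that research participation adds no commitment, so a request after early stopping should be squared with that statement. The reported effect may be smaller. Treatment and sample size do not change.

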### Study Design

This study will have a natural design. Therefore, all participants who consent to the trial will receive the same individualized treatment modality as part of the IACP. The study will be an uncontrolled, pre- and posttest trial (Figure 1), comparing measures collected at baseline to measures collected at the end of treatment within participants.

**Figure 1 figure1:**
[figure not shown]
Experimental design of the 6- to 8-week IACP for adolescents (12-18 years) with eating disorders. EOT: end of treatment; EP: extended program.

### Data Collection

Data will be collected at baseline (clinical and demographic information and preintervention self-report questionnaires), weekly (youth and parent satisfaction questionnaires), and immediately after the end of treatment (postintervention self-report and satisfaction questionnaires), as outlined in Figure 1. The clinical program coordinator will be responsible for collecting all data, deidentifying the data, and sending all deidentified data (including only participants’ random study ID) to the research team. Data to be collected include demographic and clinical information at baseline, growth curve charts, BMI pre- and postintervention, self-report standardized outcome questionnaires, acceptability (satisfaction) surveys, and measures of feasibility. All self-report questionnaires and surveys will be completed either on paper (if participants are present on site) or web-based (on a laptop or smartphone) using password-protected interactive PDF format questionnaires that will be sent to the participants using a secure email address.

Demographic and clinical information at baseline, including age, sex, level of education, diagnosis, presenting ED symptoms, duration of illness, ED treatment history (including past hospitalizations), maximum and minimum weight, comorbid symptomatology, and past medical history, will be collected by the clinical program coordinator during the intake visit for the IACP.

BMI will be calculated at baseline and at the end of treatment. Weight (with clothing on but without coats, shoes, boots, or cold weather accessories) and height (without shoes) will be measured during the first and last appointments with the clinical team using an electronic scale and a standard wall measuring scale. BMI will be calculated by dividing body weight in kilograms by the square of the height in meters.

Feasibility data will be collected by the IACP clinical staff throughout the duration of the study and will include recruitment and retention rates, in addition to measures of adherence to the protocol (Table 1).

**Table 1 table1:** Summary of feasibility measures.

Outcome	Target
Recruitment rate	80% (100/120) of eligible participants (ie, of all adolescents participating in the IACP^a^) will enroll in the study and complete the baseline measure.
Retention rate	≤25% (25/100) of enrolled participants lost to follow-up.
Adherence to protocol	At least 70% (70/100) of participants complete at least one therapeutic session per week of treatment in the IACP. At least 70% (70/100) of participants complete all pre- and postintervention questionnaires. At least 70% (70/100) of participants complete at least one therapeutic session per week and all pre- and postintervention questionnaires.

^a^IACP: Intensive Ambulatory Care Program.

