**Results:**

Rolling recruitment will take place from winter 2022 to fall 2023, during which time we expect to recruit approximately 80% (100/120) of eligible participants, retain at least 75% (75/100) of enrolled participants and have at least 70% (70/100) of enrolled participants complete at least one therapeutic session per week and all pre- and postintervention questionnaires. Data collection will occur concurrently. We base our recruitment and retention estimates on previous literature and consider that the highly flexible design of the IACP and the fact that no extra work will be required of individuals in the program to participate in the study, will lead to high levels of feasibility. We anticipate that participants and their families will be satisfied with both the program and hybrid delivery format. We expect that participation in the IACP will be associated with a medium effect size reduction in ED psychopathology from baseline to end of treatment. The data analysis and manuscript writing are expected to be completed by the summer of 2024.

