### Power Calculations

Sample size estimations were performed using G*Power 3.1. Sample size estimations were performed for all analyses, and the final targeted sample size was selected so that the analysis requiring the largest number of participants could be adequately powered.

As our proposed treatment is new and the goal of this project is to collect initial data on its effectiveness, formal power analysis cannot be conducted. However, based on the literature on the effectiveness of specialized ED care [13-15,99-104], we expect a medium effect size (f^2^=0.15). Recent work in adult patients in a specialized tertiary care ED program also showed that fully web-based care and fully in-person outpatient care both yielded a similar medium effect size [105]. Thus, we expect our hybrid model to yield medium effect sizes. This implies that the sample size required to reach a level of significance of P=.05 with a power of 0.80 is 68 participants. By testing three moderators and with an assumed dropout rate of 25% [17,42,43], we would need to recruit 98 people to test our hypotheses. Therefore, a total of 100 patients will be recruited.

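### The recruitment target pairs 80% with 100/120, but 100/120 is 83.3% and 80% of 120 is 96, so the feasibility threshold is ambiguous by four participants

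*Protocol article*

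**What the plan says.** The pair appears three times in the protocol article.

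- **Data Collection, Table 1**, in the target column for recruitment rate: "80% (100/120) of eligible participants", where eligible means taking part in the program. The row also requires completion of the baseline measure. No approximation is signalled.
- **Attrition and Compliance**: "We expect to recruit approximately 80% (100/120) of eligible participants". The same sentence restates this in words as 80% of all youth in the program, with no fraction.
- **Abstract, Results**: "we expect to recruit approximately 80% (100/120) of eligible participants".

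The planned sample is given separately under Power Calculations: "we would need to recruit 98 people to test our hypotheses", followed by "Therefore, a total of 100 patients will be recruited".

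Objectives and Hypotheses makes feasibility part of the primary objective. The Methods overview names recruitment rate as one of the three feasibility measures. Statistical Analysis summarises these measures with descriptive statistics.

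**The concern.** A percentage followed by its fraction should express one number. Here it expresses two, and the difference is too large to be rounding.

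Table 1 is where this matters most, because there the pair is a target and not a forecast. Feasibility is to be reported descriptively, so in this article the Table 1 targets are the benchmarks against which the observed rates will be judged. With two values in the cell, some results could be reported as meeting the target or as missing it, and the choice could be made after the data are seen. Those results lie at and just above the protocol's own expected rate of 80%, so the case is not remote.

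**Working it through.** **Inputs**

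- Stated percentage: 80% (Table 1; Attrition and Compliance; Abstract).
- Stated fraction: 100 of 120 (same three places).
- Planned sample: 100 (Power Calculations).

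**Step 1. Try to reproduce the stated pair.**

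- 100 / 120 = 0.833, or 83.3%. The stated 80% is not reproduced.
- 0.80 × 120 = 96. The stated 100 is not reproduced.
- Gap: 83.3 − 80 = 3.3 percentage points, or 100 − 96 = 4 participants.

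**Step 2. Compare with the other pairs in Table 1.**

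- Retention: 25/100 = 25%. Exact.
- Adherence (three entries): 70/100 = 70%. Exact.

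The recruitment row is the only one in the table whose fraction and percentage differ.

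**Step 3. Find the results on which the two readings disagree, if 120 are eligible.**

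| Enrolled of 120 | Rate | Meets 80% | Meets 100/120 |
|---|---|---|---|
| 95 | 79.2% | no | no |
| 96 | 80.0% | yes | no |
| 97 | 80.8% | yes | no |
| 98 | 81.7% | yes | no |
| 99 | 82.5% | yes | no |
| 100 | 83.3% | yes | yes |

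The readings disagree on four results, 96 to 99.

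**Step 4. Find which figures can stand together.**

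- Keep 80% and 100: 100 / 0.80 = 125 eligible.
- Keep 100 and 120: the rate is 83.3%.
- Keep 80% and 120: 96 enrolled, which no longer matches the planned 100.

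Any two of the three figures determine the third. The article states all three, and they do not agree.

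**Step 5. Check whether anything follows for sample size.** Take the least favourable combination, 96 enrolled, with the protocol's assumed 25% attrition: 96 × 0.75 = 72 completers. The base requirement under Power Calculations is "a level of significance of P=.05 with a power of 0.80 is 68 participants". Since 72 exceeds 68, no shortfall against that figure follows.

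**The case against.** The best defence is that 80% is plainly the target and 100/120 a loose illustration. The section on Attrition and Compliance restates the target in words using the percentage alone. The Table 1 row is labelled as a rate. A fraction can serve as a pass mark only if exactly 120 turn out to be eligible, which cannot be fixed in advance under rolling recruitment. Both narrative passages signal an approximation. The article gives no go/no-go rule, so no formal decision turns on 96 versus 100. A gap of 3.3 points is also well inside sampling error: the Wilson 95% interval for 96/120 runs from 72% to 86%.

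Much of this stands. It limits the consequence, and it is a good reason to treat 80% as the intended figure when making the correction. It does not make the table consistent. Table 1 carries no approximation, its other pairs are exact, and sampling error in the observed rate does not excuse an unclear benchmark.

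A reader might go further and infer that the program's planned intake is too small, because 80% of 120 gives 96 against the 98 required and the 100 planned. The article does not support that. The figure of 120 appears only inside the mismatched pair and is never given as an intake or a capacity. The apparent shortfall comes from keeping 80% and 120 while discarding 100, the one figure fixed elsewhere. It is the same mismatch counted a second time.

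**Conclusion.** The point holds as an error in a stated figure. The recruitment target, part of the assessment of a primary objective, is written as two thresholds that differ by 3.3 percentage points, or four participants if 120 are eligible.

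The arithmetic needs no assumption beyond the printed figures. The range of disputed results (96 to 99) assumes exactly 120 eligible; with another denominator the fraction has to be read as a rate of 83.3%, and the gap in percentage points is the same.

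The practical effect is small, and nothing here shows a loss of power or an inadequate intake. How the 98 under Power Calculations was reached is a separate question on which this point does not rest. A correction is still warranted, because the target will be the yardstick for a reported feasibility result and the change costs almost nothing.

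**What to change.** State one threshold, in the same form, in Table 1, in Attrition and Compliance, and in the Results part of the Abstract.

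- **Natural correction: 80% (100/125).** This keeps the percentage that the text also gives in words and the planned sample of 100. It should be made clear that about 125 is the number of eligible program participants needed to reach 100 at that rate.
- **Alternative: 83% (100/120)**, if 120 is the real projection. The restatement of 80% in Attrition and Compliance must then change as well.

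Leave the 98 and 100 under Power Calculations as they are. The 98 is presented there as resting on effect size, moderators and dropout, not on the proportion who consent. Carrying 96 into that section would put the plan below its own stated requirement and create a new contradiction.

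The cost is a change of figures in three places, with no change to recruitment, data collection or analysis.

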### Objectives and Hypotheses

The primary objective of this study is to describe the feasibility and acceptability of flexible, modular, and hybrid IACP for adolescents with EDs. Secondary aims include describing the baseline characteristics of the adolescents who enroll in the IACP, describing the preliminary effectiveness of the IACP for adolescents with EDs in an uncontrolled naturalistic setting, and describing the moderating role of age, ED diagnosis (eg, anorexia nervosa vs other ED diagnoses), length of illness, and level of attendance on clinical response to the IACP.

We hypothesize that recruiting and retaining participants in the IACP would be feasible and acceptable. We expect that participants will mostly present restrictive ED symptomatology, which is representative of the patient population seen in the ED clinic where the study will be conducted; participants will present comorbid symptomatology and ED-related behaviors, such as anxiety and depressive symptoms [31,32], high levels of affective reactivity [33] and perfectionism scores [34], poor coping [35] and self-esteem [36] skills, and high levels of social media use [37], as reported in the literature. We expect that participation in the IACP will be associated with a reduction in ED psychopathology, from baseline to the end of treatment, and that patient age, ED diagnosis, length of illness, family connectedness, and the number of hours of therapy attended will act as moderators of the preliminary effectiveness of the intervention. Although there is no consensus on moderators of treatment outcomes in the adolescent population, these moderators were chosen based on limited evidence from several reviews [8,38,39] that have identified individual, clinical, and family-related factors that are related to treatment response.

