This study has a few limitations. First, being a single-site study, recruitment will be limited to the number of patients receiving care at the study site, which may limit the final sample size and generalizability of our findings. However, it should be noted that the study will be conducted in the largest tertiary pediatric care hospital in Quebec, a Canadian province with a population of 8.5 million inhabitants. Therefore, the results of this study can be generalized to other sites in large North American urban centers. Second, the naturalistic trial design and individualized treatment approach will make it so that some of the analyses and conclusions may be impacted by external confounders (such as changes in primary treatment, seasonality, and external stressors). However, it will allow for a better understanding of the real-world feasibility and acceptability of this type of day treatment program for EDs in adolescents. Third, given the highly flexible and personalized nature of the IACP, it will not be possible to compare the feasibility and preliminary effectiveness of in-person vs web-based treatment modules. However, acceptability data (satisfaction questionnaires) may provide important clues to the participants’ appreciation of the in-person and web-based components of the program. Finally, the short duration of follow-up in this project will not allow for long-term assessment of the effectiveness of treatment in reducing ED symptomatology. Future work may include long-term follow-up of youth participating in the IACP, as well as more detailed analyses on the effectiveness of different components of the program (eg, in-person vs web-based modules).

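### Table 1's recruitment rate is research consent among adolescents already in the IACP, so it cannot show whether recruiting into the programme is feasible

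*Protocol article*

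**What the plan says.** The Objectives and Hypotheses section sets the aim: "The primary objective of this study is to describe the feasibility and acceptability of flexible, modular, and hybrid IACP for adolescents with EDs". The matching hypothesis is about the programme: "We hypothesize that recruiting and retaining participants in the IACP would be feasible and acceptable". The Methods Overview then names the recruitment rate as one of three types of rate by which IACP feasibility will be evaluated.

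Table 1 (under Data Collection) defines that rate. The denominator is "80% (100/120) of eligible participants (ie, of all adolescents participating in the IACP"), and the numerator is those who "will enroll in the study and complete the baseline measure". Attrition and Compliance glosses the denominator the same way: "80% of all youth enrolled in the IACP".

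Entry to the programme comes earlier and is a separate decision. Under Population, patients who meet the criteria are invited both to the IACP and to the research. Under Recruitment, Enrollment, and Consent, clinicians refer, a coordinator screens, and "All patients who meet the criteria for participation in the IACP will receive a brief explanation of the study". The same section makes the research optional, with no effect on IACP care. Attrition and Compliance adds: "Participation in the research study entails no additional commitment from eligible participants".

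**The concern.** The rate answers a different question from the one asked. The hypothesis concerns getting adolescents into a hybrid day programme. The measure starts once they are in it and counts how many also agree to research use of data that the programme collects anyway. Since joining the study adds no burden, a high value is to be expected and says little about whether families will take up the programme.

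A patient who meets the criteria, is invited and declines the IACP appears in no stated feasibility measure. The retention and adherence targets also start from enrolled participants. At stake is the recruitment part of the primary objective. The Future Implications section says the model could be applied at other sites if it proves feasible, and those sites would need to know what share of qualifying families accept it.

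**Working it through.** **Inputs.** From Table 1: target 80%, written as 100/120; numerator, study enrolment plus baseline completion; denominator, adolescents in the IACP. The documents give no number of youth qualifying for or declining the programme, so programme uptake *u* is an assumption and is shown as a range.

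**Step 1: the plan's own figure.**
- 100/120 = 83.3%, not 80%.
- 80% with 100 enrolled needs 100/0.80 = 125 in the programme.
- 80% of 120 is 0.80 × 120 = 96 enrolled.

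The percentage and the counts do not agree. Attrition and Compliance and the Abstract say approximately 80%, so this is a small slip. It does not affect the question of the denominator.

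**Step 2: where each measure starts.**
- Hypothesis: recruiting and retaining in the IACP.
- Table 1 recruitment rate: starts from adolescents in the IACP and counts those who join the study.
- Table 1 retention and adherence: start from those enrolled in the study.
- Referred, screened, qualifying or invited patients: the denominator of no stated measure.

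**Step 3: does the rate respond to uptake?** Let *Q* be the number who qualify and *u* the share of them who start the IACP. With 120 starting, *Q* = 120/*u*.

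- Table 1 rate = 100/120 = 83.3%, which does not contain *u*.
- Share of qualifying youth recruited to the study = 100/*Q* = 100/(120/*u*) = 0.833 × *u*.

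| Assumed uptake *u* | Qualify (*Q*) | Decline | Table 1 rate | Share of qualifying youth recruited |
|---|---|---|---|---|
| 100% | 120 | 0 | 83.3% | 83.3% |
| 90% | 133 | 13 | 83.3% | 75.0% |
| 70% | 171 | 51 | 83.3% | 58.3% |
| 50% | 240 | 120 | 83.3% | 41.7% |

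The Table 1 result is the same in every row. If consent were exactly 80%, the last column would be 0.80 × *u*, for example 40% at *u* = 50%.

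**The case against.** Several points on the other side carry weight.

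- **The hypothesis could be read differently.** It might mean recruiting IACP participants into the study, which would fit Table 1. The wording allows this, but the Methods Overview applies the rate to feasibility of the IACP itself, and the primary objective is likewise about the programme. The mismatch remains on the more natural reading.
- **A reader might infer that the whole hypothesis goes unexamined.** The documents do not support that. Table 1 has a retention target and three adherence targets, and satisfaction is surveyed weekly and at the end. The objective is to describe feasibility, the analysis is descriptive, and no formal test or go/no-go rule hangs on this rate.
- **A reader might also infer that the target could be met with a small sample and hide a shortfall.** Taken alone, 80% could be met by 40/50. But the count of 100 is printed in Table 1 and repeated in the Abstract, the recruitment section and Power Calculations. Strengths and Limitations openly warns that "recruitment will be limited to the number of patients receiving care at the study site, which may limit the final sample size". A shortfall would show.
- **Availability for all parts of the programme is an IACP eligibility criterion.** Some non-uptake is therefore classed as ineligibility, not refusal. This is true, but it means that a denominator restricted to the fully eligible would also miss these patients, so the fix has to count them.
- **An article condenses a fuller protocol.** Missing screening counts would indeed be no finding. Here, however, the article states a definition, twice and explicitly, and that definition does not fit the objective it serves.
- **The size is assumed.** It is; nothing in the documents shows that many families would decline.

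**Conclusion.** The point stands for the recruitment component only. As defined in Table 1 and in Attrition and Compliance, the rate is research consent and baseline completion among adolescents already in the IACP. It takes the same value whatever the programme uptake, so it cannot support a conclusion that recruiting into the IACP is feasible.

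The insensitivity follows from the definition and needs no assumption. Its practical size does: with uptake between 50% and 100%, the share of qualifying youth recruited would run from 41.7% to 83.3% behind a constant 83.3%. If nearly all qualifying families accept, little is lost. Separately, the printed 80% does not equal 100/120. The change is worth making because it is cheap and concerns a measure of the primary objective.

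**What to change.** In Table 1:

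1. Add an IACP uptake rate: the number starting the IACP divided by all patients who meet the clinical criteria at the coordinator's screening. Keep patients who are unavailable for all parts of the programme in that denominator. Tally those declining and those unavailable separately, with reasons.
2. Keep the present rate, which shows how well the study sample represents IACP users, but relabel it as the research-consent rate. Carry the label into Attrition and Compliance.
3. Correct its figure to 83% (100/120) or 80% (100/125), here and wherever the pair is repeated.

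The screening step already exists, so the cost is a small amount of tallying and revised wording. The downside is that the recruitment figure may look less favourable.
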